## Abstract

**Introduction:**

Hepatitis B virus (HBV) remains a public health threat and the main route of transmission is from mother to child (MTCT). Tenofovir disoproxil fumarate (TDF) treatment can reduce MTCT of HBV although the optimal timing to attain undetectable HBV DNA concentrations at delivery is unknown. This protocol describes the procedures following early initiation of maternal TDF prior to 20 weeks gestation to determine efficacy, safety and feasibility of this approach in a limited-resource setting.

**Methods and analyses:**

One hundred and seventy pregnant women from the Thailand–Myanmar border between 12 and <20 weeks gestational age will be enrolled into a one-arm, open-label, TDF treatment study with cessation of TDF 1 month after delivery. Sampling occurs monthly prenatal, at birth and at 1, 2, 4 and 6 months post partum. Measurement of tenofovir concentrations in maternal and cord plasma is anticipated in 10–15 women who have detectable HBV DNA at delivery and matched to 20–30 women with no detectable HBV DNA. Infant HBsAg status will be determined at 2 months of age and HBV DNA confirmed in HBsAg positive cases. Adverse events including risk of flare and adherence, based on pill count and questionnaire, will be monitored. Infants will receive HBV vaccinations at birth, 2, 4 and 6 months and hepatitis B immunoglobulin at birth if the mother is hepatitis B e antigen positive. Infant growth and neurodevelopment at 6 months will be compared with established local norms.

**Ethics and dissemination:**

This study has ethical approval by the Ethics Committee of the Faculty of Tropical Medicine, Mahidol University (FTM ECF-019-06), Johns Hopkins University (IRB no: 00007432), Chiang Mai University (FAM-2559-04227), Oxford Tropical Research Ethics Committee (OxTREC Reference: 49-16) and by the local Tak Community Advisory Board (TCAB-02/REV/2016). The article will be published as an open-access publication.

**Trial registration number:**

NCT02995005, Pre-results.

Strengths and limitations of this studyThis prospective cohort study will inform the optimal time to initiate tenofovir disoproxil fumarate (TDF) treatment in pregnant women to reduce hepatitis B virus (HBV) DNA to undetectable concentrations (defined as <100 IU/mL) prior to birth, which is a strength since this is currently unknown.Strategies for prevention of mother-to-child transmission (MTCT) of HIV are not immediately transferable to HBV so another strength is that this study investigates the feasibility of implementing the recommended treatment for HBV in pregnant women in a limited-resource setting.It is important to identify challenges to adherence and safety in a context of low literacy where two-thirds of pregnant women have limited education to ensure that potential implementation of this strategy is feasibleThis study investigates TDF usage during pregnancy for prevention of MTCT as a potential alternative to hepatitis B immunoglobulin (HBIG), which remains too expensive and difficult to obtain in most limited-resource settings, and will inform future studies that forgo HBIG.This study investigates TDF in addition to HBIG and vaccination in infants born to hepatitis B e antigen-positive mothers as this is the most comprehensive way to prevent MTCT, but such a design does not provide information on the proportion of MTCT in women with an undetectable HBV DNA without HBIG.

## Introduction

### Background and rationale

In 2016, it was estimated that only 1 in 10 of the 257 million people living with hepatitis B virus (HBV) were aware of their infection and of those, 1 in 7 were on treatment, which is less than 2% of the HBV infections globally.^1^ The current sustainable development goals aim to reduce the prevalence of HBV by 90% by 2030.^2^ An essential route to reach this goal is prevention of mother-to-child transmission (MTCT) of HBV, the most common source of infection. Pregnancy provides a window of opportunity in the life of an adult to advocate for a screening intervention, raising awareness of HBV infection, potentially resulting in positive impacts on prevalence. Unfortunately, both screening and prevention efforts are impeded by lack of access to universal healthcare and essential health services, a problem relevant to half of the world’s population.^3^

Maternal HBV infection is an important communicable disease on the Myanmar–Thailand border^4^ and in other parts of Asia, the western Pacific and African Region, where more than 6% of adults are infected.^1^ In antenatal clinics at the Shoklo Malaria Research Unit (SMRU) clinics, the hepatitis B surface antigen (HBsAg) prevalence is 6.4%–8.3% with a hepatitis B e antigen (HBeAg) prevalence of 32.7% in those positive for HBsAg.^4 5^ Mothers who are HBeAg positive are at the highest risk of transmitting HBV to their infants, which is the basis for specifically targeting this group for neonatal hepatitis B immunoglobulins (HBIG) within 72 hours of life. In infants born to HBeAg-positive mothers and provided HBIG and HBV vaccine, prevention of MTCT fails in an estimated 8%–32% of cases.^6^ Overall, there are two reasons to find alternatives to HBIG: (1) failure to prevent MTCT in infants born in HBeAg-positive women, and (2) for the 50% of the world’s population without universal healthcare who lack access to HBIG as it remains a specialised product that is costly, requires a cold chain and has a restrictive prescription window to be effective.^7^

The usage of antivirals for HIV in limited-resource settings has shown remarkable scale up and success and is a vital component of antenatal care (ANC) programmes.^8^ Antivirals that are active against HBV like tenofovir disoproxil fumarate (TDF) may reduce the risk of MTCT by reducing the HBV DNA across gestation to a minimum at the time of delivery when MTCT typically occurs and might be a more feasible option than HBIG in a limited-resource setting.^9^ The optimal gestational age to commence TDF is critical to know to ensure HBV DNA is as low as possible prior to birth.^10^ The precise threshold of HBV DNA, in the absence of HBIG that prevents MTCT, is also still unknown. Initially, an HBV DNA of ≥6 log10 IU/ml was associated with a higher risk of MTCT, suggesting that women in this category were the most important to target for antiviral therapy.^11–13^ Although a maternal HBV DNA <6 log10 IU/ml is thought to be lower risk for MTCT, the studies reporting this provided the infants with HBIG and vaccination. Although provision of TDF 300 mg daily in the third trimester of pregnancy significantly reduced perinatal transmission (OR 0.10; 95% CI 0.01 to 0.77; p=0.03),^6 14–16^ a mean of 8.6±0.5 weeks of TDF prior to delivery resulted in a mean HBV DNA at delivery of 4 log 10 IU/mL with 32% of mothers having HBV DNA >5.3 log 10 (or 200 000 IU/ml).^6^ This amount of HBV DNA is too high to forego HBIG, and if provided, may still not be sufficient to prevent infection. In the same study, HBV DNA declined another log (median 3.52 log10 IU/ml) in the 4 weeks post partum that TDF was provided. Gao *et al* showed that starting TDF treatment at an estimated gestational age of 24–27 weeks may achieve better suppression compared with starting in third trimester.^16^

Existing data from trials involving non-pregnant patients are not informative due to differences in age, stage of HBV, frequency of HBV DNA testing and immune response and pharmacokinetics of TDF in pregnant women compared with non-pregnant patients.^17–20^ Pharmacokinetic studies have established that the area under the curve and maximum drug concentration (C_max_) of TDF are decreased in the second and third trimester of pregnancy, and clearance is increased.^18 21–24^ In a systematic review of TDF pharmacokinetics in pregnancy, none of the manuscripts reported reaching the TDF C_max_ of 300 ng/mL the efficacy threshold determined in non-pregnant HBV infected women.^23^ These data suggest that TDF dosage and treatment initiation that are accurate for HIV and non-pregnant HBV-infected patients may not be accurate for pregnant HBV-infected women.

While some of the safety issues have been resolved with the use of TDF for prevention of MTCT of HIV, gaps remain regarding HBV.^25 26^ The main barriers to implementation of TDF are a (1) lack of knowledge by the women of hepatitis B, of their infection status, and of prevention strategies,^27^ (2) poor adherence to the prophylactic drug regimen,^9^ and (3) potential for hepatitis flares after postpartum drug discontinuation.^28^ All of these need to be evaluated and addressed in limited-resource settings where HBV is highly endemic.^29^

The aim of this prospective interventional study is to determine the appropriate time in pregnancy to initiate TDF treatment of HBV in order to reach HBV DNA <100 IU/mL at delivery. Knowing this will allow future studies where TDF can be initiated at the appropriate time so that HBIG may not be needed to prevent MTCT of HBV. The viral kinetics of HBV DNA in pregnant women receiving daily oral TDF commenced before 20 weeks gestation will be measured monthly. Infants will receive HBIG and birth-dose monovalent HBV vaccine. MTCT will be assessed at 2 months post partum. While the study population is pregnant women attending antenatal and birth services on the Myanmar–Thailand border, the study has worldwide application to women who are pregnant and HBV positive. Moreover, we will study safety, feasibility and potential barriers to implementation of TDF in routine ANC in a limited-resource setting.

### Objectives

The primary objective is to estimate the time to HBV DNA suppression <2 log10 IU/mL (or <100 IU/mL) in HBV DNA positive women who start TDF late in the first or early in the second trimester.

Secondary objectives include: estimation of the proportion of women with HBV DNA <2 log10 IU/mL (or <100 IU/mL) at delivery; the concentration of TDF in maternal and cord blood at birth in women who have detectable HBV DNA and a subset of women with undetectable HBV DNA; to monitor the safety of TDF on the Myanmar–Thailand border in pregnant women with low health literacy rates^30^ and address potential barriers to implementing TDF in early pregnancy to prevent MTCT of HBV; to determine the rate of hepatic flares post partum after cessation of TDF; to estimate the proportion of cases of vertical transmission in infants of 2 months of age; to assess fetal growth by monthly ultrasound, and infant growth at 1, 2, 4 and 6 months and neurodevelopment at 6 months.

### Study design

This is a prospective, one-arm, open-label, intervention study. Women who enrol in the study will be provided with a daily 300 mg dose of oral TDF starting at enrolment until 1 month after delivery. Follow-up will continue at 1, 2, 4 and 6 months post partum. A small subgroup of women are expected to require ongoing treatment for HBV flares and they will be followed for a further 6–9 months and provided drug therapy if required.

## Methods and analysis

### Setting

The study will be set in the clinics of SMRU on the border of Thailand and Myanmar (figure 1). Since the 1990s, the migrant influx from Myanmar to Thailand has increased for economic and political reasons, and to date there are approximately 3.5 million migrants in Thailand.^31^ Over 25% of the migrant workers have no work permits and no legal status in Thailand.^32^ Migrants are highly mobile, and the majority do not have access to basic healthcare which, combined with scarce services in Myanmar, put them at increased risk when seeking health services. In rural areas, labour migrants may be paid daily wages below Thailand’s legal minimum wage reducing health-seeking behaviours which incur cost.^33^

**Figure 1 F1:**
[figure not shown]
Map of the central office of Shoklo Malaria Research Unit in Mae Sot, and the study sites Wang Pha (WPA), Mawker Thai (MKT) and Maela (MLA) on the Myanmar–Thailand border where the study will be conducted.

SMRU has provided humanitarian healthcare for marginalised populations for 30 years. One of the original objectives was to reduce malaria-related maternal mortality from *Plasmodium falciparum* with screening embedded into routine maternal and child healthcare. The study will invite participants from three clinic sites (Mawker Thai, Wang Pha and Maela) serving marginalised populations (figure 1). The long experience of SMRU working with the population has resulted in a high level of trust in the services. The maternal and child health services are in rural areas, can be provided in Karen and Burmese language and is without costs.^5 34 35^

At the time of study protocol submission (August 2017), antiviral treatment of HBV in pregnancy was not provided by the government in Myanmar or in Thailand, although it could be obtained by out-of-pocket expenditure beyond the means of this marginalised border population.

### Study recruitment and enrolment

Pregnant women aged 16–49 years with a singleton viable pregnancy, an HBV infection, and an estimated gestational age of 12 to <20 weeks determined by ultrasound will be counselled about the disease and invited to participate in the study. Part of this information session will include counselling on HBV in general, the need for adherence to the study drug and benefits and risks of the treatment. If a woman is interested, a blood sample will be collected to determine if she meets the criteria for enrolment, that is, HBeAg positive or HBV DNA >1.9 log 10 (>85 IU/mL). Women will be informed of the results at the next visit and be enrolled and started on TDF if all inclusion criteria are met (table 1).

**Table 1 T1:** Inclusion and exclusion criteria

Inclusion criteria	Exclusion criteria
Willing and able to give informed consent for participation in the study	Negative qualitative HBV DNA if HBeAg negative
Hepatitis B infected (HBsAg confirmed positive and qualitative HBV DNA positive in HBeAg-negative mothers)	HIV positive or on immunosuppressive therapy for other illnesses
Female, 16–49 years	Elevated creatinine (>1 mg/dL)
EGA 12–20 weeks at start TDF	Abnormal serum phosphate (<2.4 and >4.5 mg/dL)
Willing to take TDF daily during pregnancy	History of kidney disease
Plans to deliver at SMRU	History of pregnancy complications

EGA, estimated gestational age; HBeAg, hepatitis B e antigen; HBsAg, hepatitis B surface antigen; SMRU, Shoklo Malaria Research Unit; TDF, tenofovir disoproxil fumarate.

SMRU has conducted research for over two decades and the trust in antenatal services is high resulting in high follow-up rates in ANC as well as in previous studies.^36^ If a woman misses an appointment, she will be contacted using her phone number if applicable or the healthcare workers will reach out to her community or family to find her.

### Follow-up

#### Medical and obstetric data

Vital signs (blood pressure, tympanic temperature, heart rate, respiratory rate, fetal heart rate); weight, height, age, symphysis fundal height, fetal gestational age; medical history review (including medications, vitamins and allergies), ethnicity, details of any past pregnancies, complications, place of delivery and outcome will be recorded; and physical examination completed (figure 2 and table 2).

**Figure 2 F2:**
[figure not shown]
Schematic reproduction of the study design. ALT, alanine aminotransferase; Cr, creatinine; EGA, estimated gestational age; HBeAg, hepatitis B envelope antigen; HBIG, hepatitis B immunoglobulins; HBsAg, hepatitis B surface antigen; HBV, hepatitis B virus; TDF, tenofovir disoproxil fumarate.

**Table 2 T2:** Overview of measurements and interventions per visit

Procedures	Visits timing						
	Start	Monthly visits	Delivery	1 month PP	2 months PP	4 months PP	6 months PP
		On TDF	On TDF	Stop TDF		End mother	End infant
Eligibility checklist	X						
Informed consent	X						
Ultrasound	X	X	X				
Demographics	X						
Medical history	X						
Physical examination	X	X	X	X		X	
**Laboratory tests**							
HBsAg/HBeAg	X						
HBV DNA	X	X	X	X			
Creatinine	X	X	X	X			
Serum phosphate	X		X				
ALT	X	X	X	X		X*	
TDF concentration			X†				
Cord HBsAg/HBV DNA			X†				
Infant HBsAg					X‡		
Pill count		X	X	X			
Adverse event assessments		X	X	X			
Infant anthropometry			X	X	X	X	X
Infant neurodevelopment							X
Adherence survey		X	X	X			
Infant HB vaccination			X§		X	X	X

*Follow-up will continue if suspected or confirmed flare.

†Cord blood sample.

‡Venepuncture sample blood and only for hepatitis B surface antigen (HBsAg).

§If mother hepatitis B e antigen (HBeAg) positive also hepatitis B immunoglobulins (HBIG).

ALT, alanine aminotransferase; HBV, hepatitis B virus; PP, post partum; TDF, tenofovir disoproxil fumarate.

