#### Monthly visits during pregnancy

From the time TDF commences, the pregnant women will return for a monthly study visit. Obstetric follow-up at each monthly visit will include vital signs, weight, symphysis fundal height measurement and fetal heart beat and concomitant medications will be recorded into the case report form (CRF). Fetal growth will be measured monthly by ultrasound (head circumference, abdominal circumference and femur length).

Adverse events (AE) will be reviewed, and reported as AE or serious AE according to the problem. Compliance will be monitored by pill counting and a questionnaire on adherence.

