#### Postpartum follow-up

TDF will be continued until 1 month post partum to decrease the risk of flares as the maternal immune system returns to baseline. All women will continue the study until the 4 month postpartum visit. At the 1 and 4 months postpartum visits, ALT will be measured. If ALT concentrations are increased, but there is not a true flare, follow-up will continue and repeat ALT testing will be done at 6 months. If the flare worsens or does not resolve, they will be placed on anti-HBV therapy and be reviewed by a physician.

All infants will be followed at 1, 2, 4 and 6 months. The infant will be screened for HBV at 2 months. At each visit, infant anthropometry will be measured (body weight, length, head circumference) and feeding recorded. At 6 months, neurodevelopment will be assessed. At months 2, 4 and 6, the infant will receive follow-up HBV vaccinations.

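### Table 2 ends general adverse event assessment at the visit where TDF stops, leaving later symptomatic maternal events and infant illness without a scheduled prompt

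*Protocol article*

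**What the plan says.** The schedule in Table 2 of the protocol article has a row for "Adverse event assessments". It is marked at the monthly visits, at delivery and at 1 month post partum, and is empty at 2, 4 and 6 months. The 1-month column is the one that marks the end of TDF.

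In the text, adverse event review appears only under Monthly visits during pregnancy: "Adverse events (AE) will be reviewed, and reported as AE or serious AE according to the problem". The section Postpartum follow-up does not mention it. That section does set how long people stay under observation. On drug: "TDF will be continued until 1 month post partum to decrease the risk of flares". For mothers: "All women will continue the study until the 4 month postpartum visit". For infants: "All infants will be followed at 1, 2, 4 and 6 months".

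Safety after TDF is a declared interest. Background and rationale lists "potential for hepatitis flares after postpartum drug discontinuation" among the main barriers to implementation, and the secondary objectives include "to determine the rate of hepatic flares post partum after cessation of TDF". The abstract places flare risk among the adverse events to be monitored. For infants, the objectives name vertical transmission at 2 months and "infant growth at 1, 2, 4 and 6 months and neurodevelopment at 6 months".

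**The concern.** The adverse event row has the same three marks as the pill count and adherence survey rows. Those two rightly end when drug supply ends. An adverse event row with the same pattern treats safety reporting as something done only while the woman is on drug, yet one of the trial's main safety questions begins when the drug is withdrawn.

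If the schedule is followed as printed, staff are not prompted to ask a mother about jaundice, other symptoms, a hospital stay or treatment elsewhere since TDF stopped. Nor are they prompted to record infant illness, admission or death after month 1. A later safety report could then not tell an absence of events from an absence of questions. This matters because the Hepatic flare section says that data on flares after stopping antivirals conflict, and that none exist in pregnant women with longer treatment.

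**Working it through.** No design figure in the article bears on this point, so the check is a comparison of the schedule with the follow-up periods.

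**Marks in Table 2 from delivery onward**

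| Row | Delivery | 1 month | 2 months | 4 months | 6 months |
|---|---|---|---|---|---|
| Adverse events | X | X | – | – | – |
| Pill count | X | X | – | – | – |
| Adherence survey | X | X | – | – | – |
| ALT (mother) | X | X | – | X | – |
| Physical examination | X | X | – | X | – |
| Infant HBsAg | – | – | X | – | – |
| Infant anthropometry | X | X | X | X | X |
| Infant neurodevelopment | – | – | – | – | X |

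**Length of the gap**

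- Mother: follow-up ends at month 4 and the last adverse event mark is at month 1. 4 − 1 = 3 months, or 3 of 4 postpartum months, all of them off TDF.
- Infant: follow-up ends at month 6 and the last mark is at month 1. 6 − 1 = 5 of 6 months. This assumes that the row covers infants at all, which the table does not say. If it covers mothers only, the infant figure is 6 of 6.

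**What is measured inside the gap**

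- *Maternal flare.* The Hepatic flare section defines it by ALT alone (above 2.5 times ULN for moderate, above 5 times for severe). ALT and a physical examination are scheduled at 4 months. Postpartum follow-up adds a repeat ALT at 6 months if ALT is raised without a true flare. A footnote to Table 2 extends follow-up for a suspected or confirmed flare, and Study design allows a further 6–9 months for women who need ongoing treatment for a flare.
- *Infant objectives.* HBsAg at 2 months, anthropometry at 2, 4 and 6 months and neurodevelopment at 6 months all fall after the last adverse event mark.

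**What is left without a prompt**

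- Maternal events that ALT at a single time point does not show: symptoms, non-hepatic events, and hepatic episodes treated elsewhere or resolved before the 4-month sample. That sample is the only scheduled maternal laboratory test between stopping TDF and the end of maternal follow-up.
- Infant illness, hospital admission or death after month 1. Anthropometry, feeding and neurodevelopment records do not capture these as events.

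**The case against.** The strongest reply is that the named safety questions are measured. Flare is an ALT endpoint, ALT is taken at 4 months with an examination, and follow-up is extended where needed. Each infant objective has its own later assessment. This stands. A reader might infer from the blank cells that nothing about safety is collected off treatment, or that the trial will report TDF withdrawal as safer than it was. The documents support neither reading. The first overlooks the ALT, examination and infant rows. The second assumes that no event is reported outside a marked cell, which the article does not say.

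It also stands that a short ALT rise between months 1 and 4 is a question of ALT sampling. Asking about symptoms could record the episode but could not classify it as a flare under the stated definition.

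A further reply is that the article is condensed, that Table 2 is an overview which omits some recorded items (infant feeding, concomitant medication), and that reporting windows belong in the full protocol. This limits the conclusion: absence from the whole plan cannot be claimed. It does not remove the point. The article is not silent here. It prints an adverse event row and fixes its visits, while other rows are filled in at 2, 4 and 6 months. If the full protocol says something different, the table misstates it.

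Finally, general infant illness is not a listed objective, and maternal follow-up ends at month 4. The second of these rules out asking for a maternal assessment at 6 months.

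**Conclusion.** The point holds in a limited form. As printed, general adverse event assessment stops at the visit where TDF stops. That leaves 3 of 4 maternal postpartum months and 5 of 6 infant months without a marked assessment. What could go unrecorded is symptomatic or non-flare maternal events in months 1 to 4, and infant illness, admission or death after month 1. ALT-defined flare at 4 months, vertical transmission, growth and neurodevelopment are not affected.

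This rests on two assumptions: that sites follow Table 2 as printed, and that the full protocol, which is not shown, has no longer reporting window. The month counts describe the schedule. They do not estimate how many events would be missed or how large any bias would be, and the article gives no figures from which to derive either. The point deserves correction because the remedy uses visits that already exist.

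**What to change.** - In Table 2, mark adverse event assessment for the mother at the existing 4-month visit, asking about symptoms, hospital contact and treatment elsewhere since TDF stopped. Ask the same at 2 months if she brings the infant; Table 2 marks no maternal procedure at that visit.
- Mark it for the infant at the existing 1-, 2-, 4- and 6-month visits, covering illness, admission and death since the last visit.
- State that the row covers both mother and infant.
- Report maternal events on TDF separately from those after TDF.
- If the full protocol already sets a longer adverse event or serious adverse event window, correct Table 2 to match it.

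The cost is a schedule correction, one CRF page and a little staff time at each existing visit, and a higher reported event count. No extra visits or blood samples are needed, and clinical management does not change.
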